### Safety analyses

Safety variables include vital signs, physical examinations, evaluation of changes to concomitant medications, clinical laboratory parameters (hematology, serum chemistry), and the incidence, timing and severity of (serious) adverse events. The severity of adverse events will be graded using the CTCAE version 5.0 dictionary.

An independent external data safety monitoring committee (DSMC) will review ongoing safety data throughout the study. Review of the safety data by the DSMC will take place based on the safety analysis after the first 6 patients. In addition, a review will be performed when the 28th patient and the last patient has ended induction treatment. Following each meeting, the DSMC will prepare a report and may recommend changes in the conduct of the trial.

### Sample size calculation and statistical analysis

In MZL a variety of treatment modalities are used. So far rituximab single agent is the most frequent chemotherapy-free approach used in this entity. Thus, a novel chemotherapy-free approach should be at least as efficient as rituximab monotherapy. In a large randomized trial rituximab monotherapy induced a CR of 55.8% compared to 78.8% for the combination of immunochemotherapy in treatment naïve EMZL subjects. CR rates in splenic MZL are comparable high at about 60%, whereas CR rates in nodal MZL are reported a rare event. As the distribution of subtypes is about 70% EMZL, 20% splenic and 10% nodal MZL, a CR which is better than 56% should at least be achieved by a new chemotherapy-free approach at 12 months after start of therapy.

For sample size calculation the one-sided one sample exact binomial test was used. According to the above data, the CR for the total group of the different subtypes must be better than 56% 12 months after start of induction therapy. Based on a CR for copanlisib of about 75%, a significance level of 2.5% (because of one-sided test) and a power of 80%, 48 full evaluable patients will be necessary to show that the combination will be a promising candidate for challenging immunochemotherapy. It is expected, that the rate of withdrawal is smaller than 15%. According to these parameters, the study is planned to enroll 56 subjects. The distribution between the sexes is not relevant, because neither incidence of MZL differed between sexes nor clinically outcome measures have been shown to be related to sexes. The primary endpoint will be evaluated 12 months after the last patient recruited has started induction treatment. The primary parameter CR will be evaluated in a modified intention to treat way, which means that all patients for whom the primary endpoint CR is measured at 12 months after start of induction will be included in the analysis of the primary endpoint (core analysis population). This analysis population consists of all eligible patients included in the study who received at least one cycle of treatment. Patients without staging 12 months after start of treatment will be defined as non-responder (CR = ‘NO’). Patients who progress before end of induction therapy will be regarded as treatment failure. No primary end point will be determined for patients who withdraw. These patients will be excluded from the confirmatory data analysis but will be analyzed in a separate exploratory sensitivity analysis of the primary end point.

The decision about the new dual treatment concept of copanlisib in combination with rituximab will be based on the one-sided one sample exact binomial test, using CR ≤ 56% as H0. Thus, claim of success can be done if 36 (75% of 48 patients) or more CR will be observed. Additionally, a one-sided 97.5% confidence interval for CR will be calculated as an effect estimator. Exploratory use of univariate logistic regression models will be performed to investigate the influence of putative risk factors associated with CR. Subgroup analysis in the subtype strata will be performed as further exploratory analysis. All secondary end points will be analyzed exploratory by respective descriptive analysis and 95% confidence intervals.

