### Key inclusion and exclusion criteria

Eligible patients must be aged ≥18 years, be able to provide written informed consent and must have a proven pathological diagnosis of either extranodal, nodal or splenic CD20-positive MZL, confirmed by a reference pathology center. Patients have to be in need of treatment and both treatment naïve and relapsed/refractory patients can be included. Treatment naïve patients have to be not eligible for local treatment or local treatment must have been failed in these patients. In patients with SMZL without splenic tissue available for histologic review, the diagnosis may be confirmed by the presence of splenomegaly and typical morphologic and immunophenotypic findings in the blood and bone marrow. At least one bi-dimensionally measurable lesion (≥1.5 cm) in its largest dimension by CT scan or MRI must be met. Of note, for gastric MZL, the clinical evidence of the MZL as seen by gastroendoscopy is sufficient. All patients should have adequate bone marrow function (neutrophil counts ≥0.75 × 10^9^*/L* or baseline platelet count ≥50 × 10^9^*/L* [if not due to bone marrow infiltration by the lymphoma], GFR ≥ 40 mL/min/1.73m^2^, AST and ALT ≤3 × upper limit of normal and bilirubin ≤2 mg*/*dL or 2 × upper limit of normal).

Main exclusion criteria include ECOG *≥*2, CNS lymphoma, histologic evidence of transformation to a high grade or diffuse large B-cell lymphoma as well as chronic active hepatitis B. Ongoing immunosuppressive therapy including corticosteroids (exception *<* 4 weeks administered at a dose equivalent to ≤40 mg*/*day prednisone is allowed) are not permitted. Additional exclusion criteria comprise an unstable or new-onset angina pectoris, myocardial infarction less than 6 months prior to test drug, congestive heart failure > class II, HbA1c > 8.5% and uncontrolled arterial hypertension despite optimal medical management.

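### The 56% null rate does not follow from the subtype mix given as its reason: the stated rates give about 51%, and 56% is the rounded treatment-naive EMZL rate, a conservative bar that is not labelled as one

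*Protocol article*

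**What the plan says.** All of the reasoning stands in the article under Sample size calculation and statistical analysis. Three rituximab CR rates are given:

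- EMZL, from one large randomised trial: "rituximab monotherapy induced a CR of 55.8% compared to 78.8% for the combination of immunochemotherapy in treatment naïve EMZL subjects".
- Splenic: "CR rates in splenic MZL are comparable high at about 60" per cent.
- Nodal: "CR rates in nodal MZL are reported a rare event", with no figure.

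The threshold is then drawn from the case mix: "As the distribution of subtypes is about 70% EMZL, 20% splenic and 10% nodal MZL, a CR which is better than 56% should" be the minimum for a new chemotherapy-free approach. The next paragraph repeats the link: "According to the above data, the CR for the total group of the different subtypes must be better than 56" per cent at 12 months. The exact binomial test takes CR ≤ 56% as H0.

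Table 1 (under Rituximab as a therapeutic strategy for MZL) gives splenic CR as 58% in 122 patients and nodal CR as 0% in 3 patients. Under Key inclusion and exclusion criteria, all three subtypes may enter, and "both treatment naïve and relapsed/refractory patients can be included".

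**The concern.** The text offers 56% as the rituximab rate to beat in the whole mixed population and gives the subtype distribution as the reason. A tenth of that population is said to have almost no complete responses, and the splenic rate is only a few points above the EMZL rate. A weighted figure therefore cannot come out equal to the EMZL rate.

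This matters because the Study rationale states the hypothesis as superiority of the combination over rituximab alone. In a single-arm trial the null rate is the only stand-in for that comparator. If 56% is not the rituximab rate for this mix, a result that misses 56% does not mean what the text implies.

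**Working it through.** **Inputs.** EMZL 55.8%, splenic about 60%, nodal rare, mix 70/20/10, H0 56%, alternative 75%, one-sided alpha 2.5%, power 80%, 48 evaluable patients (all from Sample size calculation and statistical analysis). Splenic 58% and nodal 0% (3 patients) come from Table 1. Assumption: *rare* is taken as 0%, with a range of 0-10%.

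**1. The plan's own sample size.** For the exact test, take the smallest n whose cut-off r satisfies P(X ≥ r | p0) ≤ 0.025 and P(X ≥ r | 0.75) ≥ 0.80.

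- p0 = 55.8%: n = 48, r = 34, alpha 0.0239, power 0.8001. This matches the stated 48.
- p0 = 56.0%: at n = 48, r = 34 has alpha 0.0255, which is too large. The smallest n is 51 (r = 36, alpha 0.0236, power 0.815).

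The stated 48 is what the unweighted EMZL rate of 55.8% produces. Nearby values such as 55.5% and 55.9% also give 48, so this is consistent with that origin but does not prove it.

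**2. The benchmark from the stated mix.** Benchmark = 0.70 × EMZL + 0.20 × splenic + 0.10 × nodal.

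- Stated rates, nodal 0%: 39.06 + 12.00 + 0 = **51.06%**
- Splenic 58%, nodal 0%: 39.06 + 11.60 + 0 = 50.66%
- Splenic 60%, nodal 10%: 39.06 + 12.00 + 1.00 = 52.06%

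**3. What would be needed for 56%.**

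- Nodal CR: (56 − 39.06 − 12.00) / 0.10 = 49.4%
- Or, with nodal at 0%, EMZL CR: (56 − 12.00) / 0.70 = 62.9%

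A nodal rate near one half is not a rare event, and neither EMZL series in Table 1 (45% and 56%) reaches 63%.

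**4. Dependence on the mix.** With no nodal patients and the other two subtypes in their stated proportions, the benchmark is (39.06 + 12.00) / 0.90 = 56.7%. So 56% is close to the right figure for a trial without nodal disease, but not for the mix the text names.

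**5. Consequence at 48 patients.** One-sided exact p = P(X ≥ x | p0):

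| CRs of 48 | Observed CR | p against 56% | p against 51.06% | p against 52.06% |
|---|---|---|---|---|
| 32 | 66.7% | 0.088 | 0.021 | 0.029 |
| 33 | 68.8% | 0.050 | 0.010 | 0.014 |
| 34 | 70.8% | 0.026 | 0.004 | 0.006 |

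All three results miss 56% at the 2.5% level and pass 51.06%. At the upper end of the assumed nodal range (52.06%), 32 no longer passes; 33 and 34 still do.

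**6. Direction of the error.** If the true CR rate were 51.06%, the chance of meeting the printed success rule would be P(X ≥ 36 | 48, 0.5106) = 0.0006.

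**The case against.** The best defence is that 56% is a deliberately demanding bar. The text speaks of a minimum to be achieved and ties success to challenging immunochemotherapy; it never mentions a weighted mean; and EMZL and splenic disease, with rates near 56%, make up 90% of the stated mix. A bar above the mix-based rate is safe, since it cannot produce a false success. All of this stands as a reason to keep 56%. It does not rescue the derivation, because the text presents the number as following from the distribution and from the preceding data, and nowhere says that it was set higher on purpose.

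It is also fair to say that the nodal rate is barely known: with 0 of 3, the exact two-sided 95% upper limit is 1 − 0.025^(1/3) = 71%, so Table 1 alone cannot exclude 49%. The case against 49% rests on the article's own description of nodal CR as rare, and for that reason a range is shown.

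Subtype analyses and logistic regression on risk factors are already planned as exploratory, so the case mix is not overlooked. What is missing is a benchmark that matches it.

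Some stronger readings are tempting but not supported:

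- **That the trial loses much power through the wrong benchmark.** At 48 patients, exact power at 75% is 69.9% against 56.0% and 93.0% against 51%. Part of that gap comes from rounding 55.8% up to 56%, which moves the cut-off from 34 to 35; at 55.8% the power is 80.0%.
- **That the benchmark should be lower still because Table 1 also has an EMZL series with 45% CR.** Using the randomised trial is a stated choice of source; pooling would be a preference.
- **That enrolling relapsed/refractory patients biases the comparison by some known amount.** The documents give no rituximab CR rate for relapsed MZL, so neither the size nor the direction can be derived.

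The printed success count of 36 of 48, which differs from the exact cut-off of 35 at 56%, is a separate matter.

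**Conclusion.** The point holds as an error in the derivation of the null rate, with a consequence for interpretation. On the article's own inputs the rituximab benchmark for the stated mix is about 51% (50.7% to 52.1%, assuming nodal CR of 0-10% and splenic CR of 58-60%). The 56% used as H0 is in substance the treatment-naive EMZL rate, applied to a trial that also enrols nodal, splenic and relapsed/refractory patients.

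A reader might infer that the primary test is invalid or that the type I error is inflated. The documents do not support that: 56% is stricter than 51%, so the error is conservative. A reader might equally infer that H0 should be lowered to 51%. Nothing here requires that. What needs correcting is the meaning of a missed test: 32 to 34 CRs in 48 would fail against 56% and would wrongly be taken to show no advantage over rituximab in this mix. The result for 32 is sensitive to the nodal assumption; those for 33 and 34 are not, within the range shown.

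**What to change.** 1. Correct the derivation: state that the 70/20/10 mix and the cited rates give about 51%, and name the nodal rate that was assumed.
2. State that 56% is kept as a deliberately conservative confirmatory bar equal to the treatment-naive EMZL rate, and that missing it would not show that the combination is no better than rituximab in the mixed population.
3. Report the observed CR rate and its confidence interval next to the benchmark standardised to the subtype mix actually enrolled, using the cited EMZL and splenic rates and a sensitivity range for the nodal rate. Label this descriptive and say in advance that it cannot replace a failed primary test. Without that statement, a second and lower mark would invite a rescue claim.

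The cost is a few sentences and one descriptive comparison on data already collected. The confirmatory hypothesis and the number of patients stay as they are.

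### With the stated exact test and null, 48 evaluable patients give 69.9% power, not 80%

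*Protocol article*

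**What the plan says.** All inputs stand in the protocol article, section 'Sample size calculation and statistical analysis'.

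- Planning method: "For sample size calculation the one-sided one sample exact binomial test was used". The same test is named for the final decision.
- Null: "using CR ≤ 56% as H0". The planning text gives the same figure: "the CR for the total group of the different subtypes must be better than 56% 12 months after start of induction therapy".
- Alternative: "Based on a CR for copanlisib of about 75" per cent.
- Level, power and size: "a significance level of 2.5% (because of one-sided test) and a power of 80%, 48 full evaluable patients will be necessary".
- Decision rule: "claim of success can be done if 36 (75% of 48 patients) or more CR will be observed".
- Loss: "It is expected, that the rate of withdrawal is smaller than 15" per cent, which leads to 56 enrolled.

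**The concern.** For an exact binomial test, the null rate, level and number of patients fix the critical value, and the alternative then fixes the power. The section gives every one of these, so the power claim can be checked without any further document. It does not reproduce: the stated 80% belongs to a cut-off that the stated test does not allow.

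This is the only confirmatory test in a single-arm trial. If power is about 70%, a negative result is weaker evidence against the combination than the protocol leads its readers to think.

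**Working it through.** **Inputs.** p0 = 0.56, p1 = 0.75, one-sided α = 0.025, n = 48, exact binomial test.

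**Formulas.** For X ~ Binomial(n, p):
- type I error of the rule 'k or more CRs' = P(X ≥ k | n, p0)
- critical value = smallest k for which this is at most 0.025
- power = P(X ≥ k | n, p1)

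**Step 1: where the stated 80% comes from (n = 48).**

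| Success if CRs ≥ | Type I error at 56% | Power at 75% | Within 2.5%? |
|---|---|---|---|
| 34 | 2.55% | 80.01% | no |
| 35 | 1.20% | 69.9% | yes |
| 36 (written rule) | 0.52% | 57.7% | yes |

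The figure of 80% is found only in the first row, which breaks the level. The planned one-sided 97.5% confidence limit agrees: for 34 of 48 the exact (Clopper-Pearson) lower limit is 55.94%, which does not exclude 56%.

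**Step 2: size of the error.** Type II error at the valid cut-off is 1 − 0.699 = 0.301, against 0.20 planned; 0.301/0.20 ≈ 1.5. Under the written rule it is 1 − 0.577 = 0.423.

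**Step 3: how many patients the stated test needs.**

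| Evaluable n | Critical value | Type I error | Power |
|---|---|---|---|
| 48 | 35 | 1.20% | 69.9% |
| 49 | 35 | 1.96% | 77.5% |
| 50 | 36 | 1.49% | 74.8% |
| 51 | 36 | 2.36% | 81.5% |
| 52 | 37 | 1.82% | 79.1% |
| 53 | 38 | 1.39% | 76.6% |
| 54 | 38 | 2.18% | 82.8% |
| 55 | 39 | 1.69% | 80.6% |
| 56 | 40 | 1.30% | 78.3% |
| 57 | 40 | 2.02% | 84.0% |

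The smallest n with at least 80% is 51. Because the test is discrete, power falls below 80% again at 52, 53 and 56, and stays above it only from 57.

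**Step 4: can another method give 48?**
- Normal approximation: [(1.960·√(0.56·0.44) + 0.842·√(0.75·0.25)) / 0.19]² = 49.5, so 50 patients.
- Arcsine approximation: 48.3, so 49 patients.
- Exact test with p0 = 0.558: the cut-off of 34 has type I error 2.39% and power 80.01%, and 48 is the smallest n reaching 80%.

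Only the last of these reproduces 48.

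**The case against.** **The null was 55.8%.** The same section reports the source rate: "In a large randomized trial rituximab monotherapy induced a CR of 55.8" per cent. With that null, 48 patients, the exact test, 2.5% and 80% all agree, so the likely cause (an inference) is that the size was computed at 55.8% and the text then rounded to 56%. This explains the figure but does not rescue it. The section gives 56% both in the planning text and as the formal null. A result of 34 of 48 would succeed against 55.8% and fail against 56%.

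**The shortfall sits on a step of a discrete test.** This is true: 34 misses the level by only 0.05 percentage points, and 69.9% is the lowest power for any n from 48 to 56. The alternative is also only approximate; with the cut-off of 35, power is 75.3% at a true rate of 76% and 80.3% at 77%. More than 48 patients may prove evaluable. But the protocol plans on 48, writes its success rule for 48, and bases its power on 75%.

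**69.9% is not the power of the written rule.** This also stands. The written rule has 57.7%, so 69.9% is the more favourable figure and assumes that the rule is corrected to the exact critical value.

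**Type I error is not inflated.** Correct: the written rule is conservative. The defect lies in the power claim alone.

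**Conclusion.** The power statement is wrong as written. With the exact one-sided test at 2.5%, a null of 56%, an alternative of 75% and 48 evaluable patients, power is 69.9%, about 10 percentage points below the stated 80%. The smallest number of evaluable patients that reaches 80% is 51. Neither the stated test (69.9%) nor the stated threshold (57.7%) delivers the planned power at 48.

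The result takes the document's null and alternative at face value and rests on no outside figure. It would change only if the formal null were 55.8%, and the document says otherwise.

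**What to change.** Correct the sample size paragraph so that null, evaluable number, critical value and power agree. Two restatements keep the 56% null and the 56 enrolled:

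1. **Keep 48 evaluable.** State a critical value of 35, type I error 1.20% and power 69.9%. This is the simpler and firmer correction.
2. **Raise the evaluable target to 51.** State a critical value of 36, type I error 2.36% and power 81.5%. The tolerated loss becomes (56 − 51)/56 = 5/56 = 8.9% in place of just under 15%. The weakness is that the final evaluable number cannot be chosen: at 52, 53 or 56 power is 79.1%, 76.6% or 78.3%. This option should therefore come with the table of critical values and power by n.

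In either case, say whether 55.8% or 56% was used for planning, and use one null throughout. If the threshold of 36 of 48 is kept on purpose, give its power as 57.7%.

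The cost is a change of protocol and SAP wording and a less favourable power or withdrawal figure. No extra enrolment is needed.

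### The stated 80% power is not reached at 48 or 56 patients, and it falls further because the section has two opposite rules for a patient without month-12 staging and sizes for only one of them

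*Protocol article*

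**What the plan says.** Everything is in the Protocol article, section Sample size calculation and statistical analysis.

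- **Test:** "For sample size calculation the one-sided one sample exact binomial test was used", with "a significance level of 2.5% (because of one-sided test) and a power of 80" percent, "using CR ≤ 56% as H0", and an alternative described as "Based on a CR for copanlisib of about 75" percent.
- **Evaluable number:** "48 full evaluable patients will be necessary".
- **Enrolment:** "It is expected, that the rate of withdrawal is smaller than 15%. According to these parameters, the study is planned to enroll 56 subjects".
- **Unstaged patients:** "Patients without staging 12 months after start of treatment will be defined as non-responder (CR = ‘NO".
- **Withdrawn patients:** no primary endpoint is determined for them. They are left out of the confirmatory analysis and appear only in an exploratory sensitivity analysis.
- **Core population:** described in two ways, as the patients whose CR is measured at month 12 and as all eligible patients given one cycle or more.
- **Success:** 36 or more CRs, a count derived as 75% of 48.

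**The concern.** Adding 8 patients to 48 replaces lost patients one for one. Power is protected only if each loss leaves the denominator. A patient coded as a non-responder stays in it as a certain failure, so the rate under test falls below 75%.

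The section applies both treatments. Exclusion covers patients who withdraw; failure coding covers patients without month-12 staging. Someone who withdraws before month 12 will usually meet both descriptions. The section neither defines withdrawal so as to separate the groups nor says which rule takes precedence. If the groups are in fact separate, the 15% allowance is for withdrawal alone and nothing is set aside for patients who stay in the trial but miss the staging.

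The trial has one arm and is decided by one test. A combination with a true 75% CR rate among staged patients could miss the bar because of missing assessments, while readers believe its power is 80%.

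**Working it through.** **Inputs** (all from the section): H0 rate 0.56, alternative 0.75, one-sided level 0.025, 48 evaluable, 56 enrolled, withdrawal below 15%, printed cut-off 36. My assumptions: 0.75 is the CR rate among staged patients, and loss is unrelated to response.

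**Step 1: enrolment.** 48 × 1.15 = 55.2, rounded up to 56. Equally, 56 − 8 = 48 and 8/56 = 14.3%, which is below 15%. Dividing instead, 48/0.85 = 56.5, gives 57. The 56 is reproduced, as an allowance of 8 excluded patients.

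**Step 2: power at 48 and 56.** Let c(n) be the smallest c with P(X ≥ c | n, 0.56) ≤ 0.025. Power is P(X ≥ c(n) | n, 0.75).

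| n | cut-off | size | power |
|---|---|---|---|
| 48 | 35 (exact) | 0.0120 | 69.9% |
| 48 | 36 (printed) | 0.0052 | 57.7% |
| 51 | 36 (exact) | 0.0236 | 81.5% |
| 56 | 40 (exact) | 0.0130 | 78.3% |

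The named exact test does not give 80% at 48. It first does so at n = 51 and stays at or above 80% only from n = 57. Approximations come close to 48:

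- Arcsine: h = 2·asin√0.75 − 2·asin√0.56 = 0.4033, and (1.960 + 0.842)²/h² = 48.3.
- Normal: [(1.960·√(0.56·0.44) + 0.842·√(0.75·0.25))/0.19]² = 49.5.

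**Step 3: how the 8 planned losses are classified.** Suppose k are excluded and 8 − k stay as failures. Then n = 56 − k, the 48 staged patients supply all the CRs, and power is P(X ≥ c(56 − k) | 48, 0.75).

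| excluded / non-responder | n | exact cut-off | power |
|---|---|---|---|
| 8 / 0 | 48 | 35 | 69.9% |
| 7 / 1 | 49 | 35 | 69.9% |
| 6 / 2 | 50 | 36 | 57.7% |
| 4 / 4 | 52 | 37 | 44.5% |
| 2 / 6 | 54 | 38 | 31.6% |
| 0 / 8 | 56 | 40 | 11.9% |

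The decline goes in steps because the cut-off is a whole number.

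**Step 4: the same at N = 56 with random loss.** If nobody is excluded and a random fraction d is unstaged, power is P(X ≥ 40 | 56, 0.75(1 − d)): 78.3% at d = 0, 55.5% at 5%, 31.9% at 10% and 16.5% at 8/56. The 5% and 10% are illustrations; the section gives no expected unstaged fraction.

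**Step 5: all 8 excluded, plus further unstaged patients.** Among the remaining 48, with cut-off 35 and u coded as failures, power is P(X ≥ 35 | 48 − u, 0.75): 61.0% for u = 1, about 51% for u = 2 and 30.9% for u = 4.

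**Step 6: the fixed 36.** P(X ≥ 36 | 56, 0.56) = 0.132. A count of 36 keeps the 2.5% level at n = 48 but not at n = 56.

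**The case against.** The strongest reply is that the only loss the section plans for is withdrawal, and it removes withdrawn patients from the confirmatory analysis. On that reading the step from 48 to 56 matches the handling of the loss it was meant for. This stands. A reader might infer that power drops to about 16% at the loss the plan expects. The document does not support that: the figure needs no exclusions at all and every one of the 8 planned losses coded as a failure. It is one end of a range.

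Two further replies have some force. First, an assumed CR rate of roughly 75% could already count unstaged patients as failures, which is an ordinary design choice. But the section attaches the rate to evaluable patients and does not say so; even then, power at 56 with nobody excluded is 78.3%. Second, the section prints a cut-off of 36, not 40. With 36 of 56 and random loss at 8/56 coded as failure, the chance of passing would be 56%, but the type I error would be 13.2%, so this does not rescue the stated design.

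The replies do not remove the overlap between the two rules. They also do not restore 80%: the reading most favourable to the sponsor gives 69.9% at 48.

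**Conclusion.** The point holds in a limited form and should be corrected.

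- The printed 80% is not what the named exact test gives. It is 69.9% at 48 (57.7% with the printed cut-off of 36) and 78.3% at 56 without loss.
- The section has two opposite rules that can apply to the same patient, and the sizing provides for exclusion only. Depending on how 8 losses are classified, power runs from 69.9% down to about 12% (16.5% if loss is random at 8/56).
- The low end is the worst case. Where the trial would fall cannot be told from the document, because it gives no expected number of unstaged patients who did not withdraw.

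The figures rest on a 75% CR rate among staged patients, loss unrelated to response, and a cut-off recomputed for the number analysed. The enrolment arithmetic itself is not in error, and nothing here shows that either rule for missing staging is the wrong one.

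**What to change.** In the sample size section:

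1. State which rule governs a treated patient without month-12 staging, naming explicitly the patient who withdrew, and give one definition of the core population to match.
2. State whether the 75% counts unstaged patients as failures.
3. Replace 80% with the exact power under that rule, over a plausible range of losses.
4. State the success cut-off as the exact critical value for the number actually analysed (35 of 48, 40 of 56) instead of a fixed 36.

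Enrolment can stay at 56. The cost is wording and a less favourable stated power; no patients or procedures are added.

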### Treatment

Patient enrollment started in November 2019. Eligible patients receive an induction phase of copanlisib and rituximab followed by a maintenance phase of each test drug (Fig. 2). The induction phase consists of six cycles (1 cycle = 28 days). Copanlisib will be administered intravenously at a fix dose of 60 mg on days 1, 8, 15 of each cycle. Rituximab will be applied intravenously at a dose of 375 mg/m^2^ only on day 1 of each cycle.

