**Fig. 2 Fig2:**
[figure not shown]
Trial design. i.v. = intravenous

Maintenance starts 2 months after the last induction cycle for patients at least achieving a stable disease after induction. During maintenance time copanlisib is administered at a dose of 60 mg on days 1 and 15 every 4 weeks for a maximum of 12 cycles. Rituximab application is scheduled at a dose of 375 mg/m^2^ every 8 weeks for a maximum of 12 infusions unless progression or study drug-related intolerable toxicity. In the follow-up phase, all subjects who enter the trial will continue to be followed every 3 months for disease progression, subsequent treatment and survival for 2 years after completion*/*discontinuation of treatment. Subsequently, patients will be monitored every 6 months for three additional years.

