### Study objectives

The objective of the trial is to test the efficacy and toxicity of treatment with copanlisib and rituximab in patients with MZL in need of treatment, who have failed, are not eligible for local therapy or relapsed. The primary end point of this study is the CR rate determined 12 months after start of induction therapy. For efficacy the rate of complete remissions according to the GELA criteria for gastric MZL or to the Cheson 2007 criteria for non-gastric extranodal, nodal and splenic MZL will be primarily analysed. Secondary efficacy end points include response rates (CR, PR and OR [CR or PR]), best response, time to best response, time to first response, progression-free survival, time-to-treatment failure, remission duration, cause specific survival and overall survival. Quality of life assessment, based on the functional assessment of cancer therapy for lymphoma version 4 (FACTLym) will be measured before start of treatment, during induction and maintenance.

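### The failure rule stops at the end of induction although CR is read at month 12, and no stated rule sets a CR reached on non-protocol therapy to CR = NO.

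*Protocol article*

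**What the plan says.** Under Study objectives, the protocol article states: "The primary end point of this study is the CR rate determined 12 months after start of induction therapy". Response is judged by GELA criteria in gastric disease and by Cheson 2007 criteria otherwise.

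Under Sample size calculation and statistical analysis, three rules decide how patients enter the primary analysis:

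- Missing staging: "Patients without staging 12 months after start of treatment will be defined as non-responder (CR = ‘NO".
- Progression: "Patients who progress before end of induction therapy will be regarded as treatment failure".
- Withdrawal: "No primary end point will be determined for patients who withdraw". These patients are left out of the confirmatory analysis and appear only in an exploratory sensitivity analysis.

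Under Treatment, induction is six cycles of 28 days. In the text below Fig. 2, maintenance is for patients with at least stable disease and can end early for progression or intolerable toxicity. The same text says of follow-up that "all subjects who enter the trial will continue to be followed every 3 months for disease progression, subsequent treatment and survival".

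**The concern.** The progression rule and the endpoint refer to different times. The rule treats progression as decisive whatever is seen later, but only up to the end of induction. The endpoint is read about half a year after that. The opening of Methods and study design shows the same mismatch: it places the CR analysis after induction, while Study objectives and the sample size section place it at month 12.

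The patient who matters stops copanlisib and rituximab before month 12, starts another anti-lymphoma therapy and is in CR when staged at month 12. None of the three rules clearly makes this patient a non-responder. There are two possible outcomes:

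- The patient is counted as a CR, and the study regimen is credited with the effect of another treatment.
- The patient is regarded as withdrawn, a term the article does not define against progression or new therapy, and leaves the denominator.

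The first raises the number of CRs. The second raises the observed rate by removing a patient whom the regimen did not bring to a lasting CR. A single-arm trial tested against a fixed 56% has no control group in which the same error could offset this.

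**Working it through.** **Inputs from the article:** endpoint at month 12; induction 6 × 28 days; H0 CR ≤ 56%; expected CR 75%; one-sided exact binomial test at 2.5%; 48 evaluable patients; success at 36 or more CRs. **Not in the article:** the share of patients who start other therapy before month 12 and are then staged in CR. This is varied below as an assumption.

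**1. Time outside the progression rule.** 6 × 28 = 168 days, about 5.5 months. 365 − 168 = 197 days, and 197/365 = 54% of the period before the endpoint is read. New therapy is not covered at any time in the 12 months.

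**2. The plan's decision rule.** With X ~ Binomial(48, 0.56), the p-value for r CRs is P(X ≥ r):

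| CRs of 48 | Exact p | H0 rejected at 2.5% | Success at stated boundary (36) |
|---|---|---|---|
| 33 | 0.0495 | no | no |
| 34 | 0.0255 | no | no |
| 35 | 0.0120 | yes | no |
| 36 | 0.0052 | yes | yes |

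The exact test already rejects at 35, so the stated boundary of 36 is stricter than the test requires. It has 57.7% power at a CR rate of 75%, not the stated 80%. How N, boundary and power fit together is a separate matter and does not affect this point.

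**3. Counting CRs from other therapy.** Each one adds 1/48 = 2.1 percentage points. Suppose 36 CRs are counted. If one came from other therapy, the regimen's own result is 35/48 (p = 0.0120), which passes the test but misses the stated boundary. If two did, it is 34/48 (p = 0.0255), and H0 is not rejected.

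**4. Effect on the false-success probability.** Let the true CR rate on the regimen be 56%, and let a further share q of all patients be wrongly counted as CR. The chance of success is then P(X ≥ r) with X ~ Binomial(48, 0.56 + q):

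| q (assumed) | Patients of 48 | r = 36 (stated) | r = 35 (exact 2.5% limit) |
|---|---|---|---|
| 0% | 0 | 0.5% | 1.2% |
| 2% | 1.0 | 1.1% | 2.4% |
| 4% | 1.9 | 2.2% | 4.4% |
| 6% | 2.9 | 4.1% | 7.7% |
| 8% | 3.8 | 7.3% | 12.7% |
| 10% | 4.8 | 12.1% | 19.6% |

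**5. Excluding the patient as a withdrawal.** Take 34 CRs among 48, where one of the 14 without a CR on the regimen had switched therapy. Counted as CR = NO, the result is 34/48, p = 0.0255. Excluded, it is 34/47, p = 0.0160, and H0 is rejected. Exclusion therefore helps under the exact test. It does not help under a fixed count of 36, because the number of CRs is unchanged.

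**The case against.** The strongest objection is that an article condenses the protocol, and the handling of non-protocol therapy often stands in the full protocol or the SAP. Silence on new therapy alone would be no finding. But the article does state a progression rule, and it ties that rule to a time other than that of the endpoint. An analysis plan that followed the sentence literally would carry the gap forward. The full documents may already close it, and then only the published sentence needs aligning.

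Three stronger readings are tempting, and the article does not support them.

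- A reader might infer that any patient who progresses between induction and month 12 can still be counted as a CR. Progression without other therapy would normally not meet GELA or Cheson CR at month 12, and a patient without staging is already a non-responder. The exposed group is patients who start other therapy, with or without prior progression.
- A reader might infer that patients off study treatment will usually be staged at month 12. The follow-up text names progression, subsequent treatment and survival every 3 months after treatment ends. It sets out no restaging schedule for these patients that is tied to month 12. Such staging is possible, but how often it would occur is unknown.
- A reader might take the exact test alone and conclude that moving from 33 to 35 CRs would change the trial's decision. It crosses the test's 2.5% limit but not the stated boundary of 36.

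The withdrawal rule may also keep some of these patients from being counted as CRs. That stands, but exclusion carries its own bias (step 5).

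**Conclusion.** The point holds for patients who receive non-protocol anti-lymphoma therapy before month 12. As written, they can be counted as CRs of the study regimen or dropped from the denominator, and neither outcome counts against the regimen.

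The size cannot be fixed from the article. It depends on how many patients switch, respond completely and are staged by month 12, and no rate is given for any of these. Under the stated assumptions, two such patients separate a result that does not reject H0 (34/48) from a declared success (36/48). The strict boundary of 36 gives some protection: the false-success probability is still 2.2% when 4% of patients are wrongly counted, and passes 2.5% somewhere between 4% and 6%. If the exact limit of 35 were used, it would be just under 2.5% at 2% and above it at 4%.

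This should be corrected. It does not show that a positive result would be wrong.

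**What to change.** Replace the progression sentence under Sample size calculation and statistical analysis with:

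> Patients with progression, or who start any non-protocol anti-lymphoma therapy, at any time before the month-12 staging are counted as CR = NO in the primary analysis; this rule takes precedence over the exclusion of patients who withdraw.

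The last clause is needed because otherwise the same patient could fall under two rules. This is an analysis rule only and changes nothing in how patients are treated or followed. The time of the CR analysis in Methods and study design should be brought into line with month 12 in the same edit.

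The cost is one sentence in the protocol and SAP. Progression and subsequent treatment are already recorded in follow-up, and the sample size and boundary do not change. The drawback is that the observed CR rate may be slightly lower, and with it the chance of reaching 36.
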